## Abstract

**Background:**

Tactile maneuvers stimulating spontaneous respiratory activity in preterm infants are recommended since birth, but data on how and how often these maneuvers are applied in clinical practice are unknown. In the last years, most preterm newborns with respiratory failure are preferentially managed with non-invasive respiratory support and by stimulating spontaneous respiratory activity from the delivery room and in neonatal intensive care unit (NICU), in order to avoid the risks of intubation and prolonged mechanical ventilation.

**Methods:**

Preterm infants with gestational age < 31 weeks not intubated in the delivery room and requiring non-invasive respiratory support at birth will be eligible for the study. They will be randomized and allocated to one of two treatment groups: (1) the study group infants will be subject to the technique of respiratory facilitation within the first 24 h of life, according to the reflex stimulations, by the physiotherapist. The newborn is placed in supine decubitus and a slight digital pressure is exerted on a hemithorax. The respiratory facilitation technique will be performed for about three minutes and repeated for a total of 4/6 times in sequence, three times a day until spontaneous respiratory activity is achieved; thus, no respiratory support is required; (2) the control group infants will take part exclusively in the individualized postural care program. They will perform the technique of respiratory facilitation and autogenous drainage.

**Objective:**

To evaluate the efficacy of early respiratory physiotherapy in reducing the incidence of intubation and mechanical ventilation in the first week of life (primary outcome).

**Discussion:**

The technique of respiratory facilitation is based on reflex stimulations, applied early to preterm infant. Slight digital pressure is exerted on a “trigger point” of each hemithorax, to stimulate the respiratory activity with subsequent increase of the ipsilateral pulmonary minute ventilation and to facilitate the contralateral pulmonary expansion. This mechanism will determine the concatenation of input to all anatomical structures in relation to the area being treated, to promote spontaneous respiratory activity and reducing work of breathing, avoiding or minimizing the use of invasive respiratory support.

**Trial registration:**

UMIN-CTR Clinical Trial UMIN000036066. Registered on March 1, 2019. Protocol 1. https://www.umin.ac.jp/ctr

## Background

In the last years, most preterm newborns with respiratory failure are preferentially managed with non-invasive respiratory support and by stimulating spontaneous respiratory activity just after birth in both the delivery room and neonatal intensive care unit (NICU), in order to avoid the risks of intubation and mechanical ventilation. The latest European guidelines for the management of respiratory distress syndrome (RDS) recommend the early application of continuous positive airway pressure (CPAP) of at least 6 cm H_2_O from the delivery room in preterm infants, in order to improve and maintain adequate functional residual capacity (FRC) of the lungs [1, 2]. Some authors suggest the administration of caffeine already in the delivery room to stimulate the spontaneous respiratory activity of the preterm infants [2]. The combined use of CPAP and intravenous caffeine (and rescue administration of surfactant) is aimed to achieve and maintain adequate FRC of the preterm infant’s lung.

Tactile maneuvers stimulating spontaneous respiratory activity in preterm infants are recommended during the initial assessment since birth. Te Pas et al. observed a positive effect of the use of repetitive tactile stimulation on respiratory effort and oxygenation of preterm infants at birth [3]: rubbing the sole of the foot or the infants’ back supposedly activates proprioceptors or somatic/visceral mechanoreceptors in the thorax, respectively, which are known to stimulate spontaneous breathing [3]. These afferent somatosensory pathways are functional even before 25 weeks of gestation [4, 5]. To best of our knowledge, no randomized clinical trials have evaluated the efficacy of early and continued respiratory facilitation physiotherapy in avoiding or reducing the need for invasive respiratory support of preterm infants in NICU.

The aim of this study is to evaluate the efficacy of a respiratory facilitation physiotherapy technique according to reflex stimulations, applied within the first 24 h of life to preterm infants not intubated in the delivery room but requiring non-invasive respiratory support, and continued during hospital stay, to promote spontaneous respiratory activity, avoiding or minimizing the need for invasive respiratory support.

## Methods

The primary hypothesis of this study is a reduction in the need of mechanical ventilation (MV) in the first week of life (excluding the transient tracheal intubation performed for surfactant administration) in spontaneously breathing infants born at 24^+0^–30^+6^ weeks’ gestation receiving a respiratory facilitation maneuver according to the reflex stimulations compared to exclusive standard individualized postural care program.

The secondary outcome will be:

(i) Duration of mechanical ventilation (MV) during the hospital stay;

(ii) Duration of O_2_-therapy during the hospital stay;

(iii) Bronchopulmonary dysplasia (BPD): O_2_-dependence at 36 weeks of postmenstrual age;

(iv) Duration of non-invasive ventilation (NIV) during the hospital stay;

(v) Post-conceptional age attainment of complete respiratory autonomy (absence of any kind of respiratory support and oxygen);

(vi) Pulmonary atelectasis diagnosed on chest X-ray and/or lung ultrasound;

(vii) Length of hospital stay;

(viii) Survival.

Additional data recorded for each infant will include occurrence of: pneumothorax; pulmonary interstitial emphysema; pulmonary hemorrhage; hemodynamically significant patent ductus arteriosus requiring treatment with ibuprofen; grade 3–4 intraventricular hemorrhage [6]; periventricular leukomalacia worse than grade 2 [7]; retinopathy of prematurity [8]; necrotizing enterocolitis [9]; sepsis, defined as a positive blood culture or suggestive clinical and laboratory findings leading to treatment with antibiotics for at least 7 days despite absence of a positive blood culture; and use of systemic postnatal steroids.

This will be an unblinded mono-center randomized trial conducted at Fondazione Policlinico Universitario A. Gemelli IRCCS’s NICU. Eligible candidates will be preterm newborns with gestational age (GA) < 31 weeks not intubated in the delivery room and requiring non-invasive respiratory support. Exclusion criteria will be as follows: outborn, presence of major congenital malformations and/or genetic syndromes, fetal hydrops, inherited disorders of metabolism, persistent pulmonary hypertension of the newborn, severe circulatory shock (prolonged capillary filling, reduced strength of peripheral pulses, cool skin, lethargy, hypotension, oliguria, increasing lactate concentrations and metabolic acidosis), and other unstable clinical conditions at the time of randomization for which the newborn cannot perform the physiotherapy treatment required by the study.

All preterm infants managed in our NICU routinely follow routinely the program of individualized postural care [10–15], which include handling and positioning of the infant. Neonatal nurses and physiotherapists can play a major role in designing, modeling, and teaching positioning strategies that promote oxygen saturation stability, skeletal integrity, postural control, and sensorimotor organization. The individualized postural care program consists in alternating postures according to the needs of each individual infant. The postures are alternated in 24 h and are prone, supine, and lateral with adequate postural supports.

Eligible infants will be allocated during the first 24 h of life to one of the two treatment groups (Fig. 1). In the study group, the physiotherapist will perform the technique of respiratory facilitation according to the reflex stimulations, experience already conducted in the neonates [16] and modified for the preterm infant. The newborn is placed in supine decubitus and a slight digital pressure is exerted on a hemithorax, more precisely between the 7th and the 8th rib (area corresponding to the insertion of the diaphragm muscle) at the level of the mammillary line, pressing from top to bottom (in the direction of the support plane) and obliquely (in the direction of the vertebral column). We will define this as a “trigger point.” Stimulating the trigger point will stimulate the respiratory activity by determining a compression on the stimulated side with consequent increase of the ipsilateral pulmonary ventilation/minute and the facilitation of the contralateral pulmonary expansion (thoracic expansion of the ribcage). The respiratory facilitation technique will be performed for about 3 min and repeated for a total of 4/6 times in sequence: 7th right hemitoraceous space for 3 min, 7th left hemithorax space for 3 min, 7th right space for a further 3 min, and 7th left space for a further 3 min. In case of secretions, the respiratory facilitation technique will be associated with the prolonged slow expired technique for the preterm infant. This program will be performed 3 times a day until complete respiratory autonomy (absence of any kind of respiratory support and oxygen) is achieved.

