The intervention in the study group will be continued also in case of intubation and start of MV during the entire hospital stay, to enhance respiratory function and favoring extubation.

Infants of both groups will receive 200 mg/kg of poractant alfa (Chiesi Farmaceutici, Parma, Italy) if they will need FiO_2_ ≥ 0.30 and CPAP of 6–7 cm H_2_O, by IN-SUR-E technique (if gestational age ≥ 28 weeks) or IN-REC-SUR-E technique [20] (if gestational age < 28 weeks), as per our NICU protocol. The indications for mechanical ventilation will be: poor oxygenation with FiO_2_ greater than 0.40 after rescue surfactant, respiratory acidosis (pCO_2_ > 65 mm Hg [8·5 kPa] and pH < 7·20), or apnea (more than four episodes of apnea per h or more than two episodes of apnea per h requiring ventilation with bag and mask), despite optimal nasal CPAP, nasal intermittent positive pressure ventilation, or bilevel positive airway pressure.

The analysis of our NICU data for the year 2017 showed how the incidence of intubation and mechanical ventilation in the first week of life in preterm infants with GA ≤ 30 weeks, not intubated in the delivery room stands at 50%. The expected effect of the intervention proposed in the trial is an absolute risk reduction of 25% (relative risk reduction of 50%) from the expected control group rate.

Considering an α error of 0.05 (two-tailed) and a study power of 80%, 66 newborns are expected to be enrolled per arm (132 total newborns); this number will be increased by 10% to take account of any dropouts.

Statistical analysis will be carried out using the “intention to treat” method; all data will be collected in a single database and analyzed to evaluate any differences between the randomized groups both for primary outcomes and for secondary outcomes. Any associations between individual dependent and independent variables will be evaluated initially and the choice of statistical methods will be decided according to the nature of the variables (categorical, continuous, rank-order) and their distribution (normal, non-normal, other). Statistical analyses will be performed using the “Stata Statistical Software: Release 15.1 software (StataCorp LP, College Station, TX).”

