Infants will be randomly allocated in a 1:1 ratio to receive either technique of respiratory facilitation (intervention group) or individualized postural care (control group). Ralloc, a Stata/IC 15.1 for Windows (Stata-Corp, College Station, TX), will be used to provide a sequence of treatments randomly permuted in blocks of varying size and order. Allocation concealment will be ensured by sequentially numbered, opaque, sealed envelopes.

The study protocol was approved by the Ethics Committee of the Fondazione Policlinico Universitario A. Gemelli IRCCS, Rome, Italy, with the approval number 9108/18 ID: 1906. Written and oral information will, whenever possible, be offered to parents if their infant is likely to be eligible. Informed written consent will be signed from both the parents and sufficient time will be provided for consent.

We used the SPIRIT reporting guidelines [21].

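### The primary outcome leaves out death, so an infant who dies before day 7 without mechanical ventilation would, read literally, count as a favourable outcome

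*Protocol article*

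**What the plan says.** In the protocol article's Methods, the primary hypothesis is "a reduction in the need of mechanical ventilation (MV) in the first week of life". One qualification follows in brackets: "excluding the transient tracheal intubation performed for surfactant administration". The Objective in the Abstract and the sample size paragraph also describe a first-week outcome of intubation and ventilation, and neither mentions death.

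Death appears only in the list of secondary outcomes, as item "viii) Survival". The article defines no combination of ventilation and death.

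The Methods also describe a single-centre, unblinded trial in infants of 24+0 to 30+6 weeks, analysed by intention to treat.

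**The concern.** Death before day 7 prevents ventilation from being observed afterwards. The endpoint has two categories, ventilated or not. An infant who dies unventilated meets no condition for an event and therefore falls in the favourable category. The article does not state that scoring; it is what the definition yields when applied as written.

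Intention to treat does not settle the matter. It says in which arm an infant is analysed, not how the infant's outcome is scored.

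If such deaths were more frequent in one arm, that arm's ventilation rate would look better for the wrong reason. Listing survival as a secondary outcome makes the deaths visible but does not correct the primary comparison. Because the trial is unblinded, a scoring rule settled only after deaths have occurred could be influenced by knowing the arm. The article does spell out one borderline case, intubation for surfactant, so this is the natural place to settle the other.

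**Working it through.** **Inputs, all from the Methods.** Control rate 50% and "an absolute risk reduction of 25% (relative risk reduction of 50%) from the expected control group rate", hence 50% v 25%. Two-sided α 0.05, power 80%, 66 infants per arm, allocation 1:1.

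**The plan's own figure.** With z values 1.960 and 0.842 and mean rate 0.375:

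- Uncorrected: n = [1.960·√(2·0.375·0.625) + 0.842·√(0.50·0.50 + 0.25·0.75)]² / 0.25² = (1.342 + 0.557)² / 0.0625 ≈ 57.7, so 58 per arm.
- With continuity correction: n' = (57.7/4)·[1 + √(1 + 4/(57.7·0.25))]² ≈ 65.4, so 66 per arm.

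The stated 66 is reproduced with the continuity correction.

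**Result at the planned effect.** 50% of 66 is 33. 25% of 66 is 16.5, taken as 17. Pearson chi-square = N(ad − bc)² / (product of the four margins) = 132·(33·49 − 33·17)² / (66·66·50·82) = 8.24, p = 0.004.

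**Unventilated study-arm deaths re-scored as events, none in controls.** Let k be the number of such deaths among the study infants first counted as favourable. The comparison becomes 33/66 v (17 + k)/66.

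| k | Study arm | Difference (points) | p, Pearson | p, continuity-corrected | p, Fisher |
|---|---|---|---|---|---|
| 1 | 18/66 | 22.7 | 0.007 | 0.012 | 0.012 |
| 2 | 19/66 | 21.2 | 0.013 | 0.021 | 0.020 |
| 3 | 20/66 | 19.7 | 0.021 | 0.033 | 0.033 |
| 4 | 21/66 | 18.2 | 0.034 | 0.051 | 0.051 |
| 5 | 22/66 | 16.7 | 0.052 | 0.077 | 0.077 |

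Significance is lost at 5 deaths with the uncorrected test, and at 4 with the continuity correction or Fisher's exact test. The article names no test. Five deaths are 5/66 = 7.6% of the study arm, or 5/49 = 10.2% of the 66 − 17 = 49 study infants counted as unventilated.

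**The same number of deaths in both arms.** With 5 in each arm, the comparison is 38/66 v 22/66. The difference is still 16/66 = 24.2 points, and chi-square = 132·(38·44 − 28·22)² / (66·66·60·72) = 7.82, p = 0.005. The conclusion is at risk only if the deaths are unequal between arms.

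**The case against.** The strongest reply is that few infants can be affected. The Methods list poor oxygenation after surfactant, respiratory acidosis and repeated apnea as indications for ventilation, so an infant failing on non-invasive support would usually become a ventilation event before dying. Infants with major malformations, severe shock or other unstable conditions are excluded at entry. Survival is recorded, so deaths would not be hidden. All of this stands, and it is why the effect is judged small. It does not supply a scoring rule for the deaths that remain.

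A second reply is that ventilation or death is a different endpoint: the 50% control rate was derived for ventilation alone, and the trial is registered and recruiting. This also stands and shapes the fix.

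Three stronger readings are tempting, but the documents do not support them:

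- **That dropouts are left unscored and only infants who stay are analysed.** The plan says "this number will be increased by 10% to take account of any dropouts", but inflating a sample does not contradict intention to treat. The 10% is not tied to the first week, and rules for missing outcomes may sit in a full protocol or SAP that is not shown.
- **That such losses could reverse the result.** Inflating 66 by 10% gives 72.6, or 73 per arm, 7 more than 66. Suppose all 7 per arm were unscored, every missing study infant failed and every missing control succeeded. The result would be 33/73 (45.2%) v 24/73 (32.9%), p = 0.127. Significance goes, but the direction still favours the study arm.
- **That a single death could decide the trial.** This needs a result already at the boundary and depends on the test. 33/66 v 21/66 gives p = 0.034 uncorrected but 0.051 with continuity correction or Fisher, so in the latter case there is no significance left to lose.

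**Conclusion.** The point holds as a gap in the definition of the primary endpoint. As written, death before day 7 without ventilation is not an event and falls among the favourable outcomes.

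The size is probably small. At the planned effect it takes about 5 such deaths in the study arm with none in controls to lose significance (4 under a corrected or exact test), and equal numbers in both arms leave the conclusion unchanged.

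This rests on two assumptions: observed counts at the design values, and an early unventilated death rate that the article does not give. The case for acting is that the correction removes an avoidable source of bias at very little cost, not that the result is likely to turn on it.

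**What to change.** Define the primary event as mechanical ventilation or death within the first 7 days of life, for every randomised infant, keeping the existing exclusion of brief intubation for surfactant. Report ventilation alone as a supporting result, and show the number of deaths without ventilation in each arm.

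If the registered endpoint must stand because recruitment is under way, keep it and prespecify ventilation or death by day 7 as a key sensitivity analysis of the primary comparison. Date the decision before outcomes are examined by arm.

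**Cost.** No new data should be needed: first-week ventilation and survival are already outcomes. The combined event is slightly less specific to ventilation, and the 50% control rate was derived for ventilation alone, so the sample size basis should be noted as approximate for the combined event. Changing the primary outcome itself would also need a protocol amendment and a registry update; the sensitivity analysis leaves the registered primary outcome unchanged.

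### Six secondary outcomes, including BPD and length of stay, are defined without regard to death, so some can favour an arm with more deaths

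*Protocol article*

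**What the plan says.** The Methods section of the protocol article lists eight secondary outcomes. Item (iii) is "Bronchopulmonary dysplasia (BPD): O_2_-dependence at 36 weeks of postmenstrual age". Item (i) is "Duration of mechanical ventilation (MV) during the hospital stay", and items (ii) and (iv) define oxygen and non-invasive ventilation time over the same period. Item (v) is "Post-conceptional age attainment of complete respiratory autonomy", meaning no support and no oxygen. Item (vii) is length of stay. None of these six has a death component, a restriction to survivors or a competing event. Survival stands alone as item (viii).

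On analysis, the same section states: "Statistical analysis will be carried out using the “intention to treat” method". The method for each variable is to follow from its type and distribution. The population is 24+0 to 30+6 weeks' gestation on non-invasive support. No mortality or BPD rate is given.

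**The concern.** Deaths must be expected in this population, and the protocol itself lists survival as an outcome. Death prevents or cuts short the measurement of six of the eight secondary outcomes:

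- **BPD (iii):** an infant who dies before 36 weeks cannot be oxygen-dependent at 36 weeks. The infant either counts as BPD-free or leaves the comparison.
- **Length of stay (vii):** death ends the stay, so an early death yields a short one.
- **Oxygen and non-invasive time (ii, iv):** an early death stops the count.
- **Ventilation time (i):** death stops the count, but an infant may die after a long period on the ventilator.
- **Age at autonomy (v):** no value exists for an infant who dies on support, and none is reached by discharge for an infant sent home on oxygen.

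At stake is the direction of the comparison. An imbalance in deaths could appear as a lower BPD rate or a shorter stay, and so be read as respiratory benefit.

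**Working it through.** **The plan's own figure.** The sample size rests on two-sided alpha 0.05, 80% power and "an absolute risk reduction of 25% (relative risk reduction of 50%) from the expected control group rate", that is 50% v 25%.

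- Pooled formula: n' = [1.960·√(2·0.375·0.625) + 0.842·√(0.5·0.5 + 0.25·0.75)]² / 0.25² = 57.7.
- With continuity correction: n = (n'/4)·[1 + √(1 + 4/(n'·0.25))]² = 65.4, so 66 per arm.

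This matches the stated 66. It depends only on the primary outcome, so nothing below affects it.

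**Illustration 1: BPD with equal lung disease.** Both inputs are assumptions: BPD in 30% of survivors in both arms, and mortality before 36 weeks of 8% v 14%.

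| Measure | Formula | 8% mortality | 14% mortality |
|---|---|---|---|
| BPD, all randomised | 0.30·(1 − d) | 27.6% | 25.8% |
| BPD, survivors only | 0.30 | 30% | 30% |
| Death or BPD | d + 0.30·(1 − d) | 35.6% | 39.8% |

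Over all randomised infants, the arm with more deaths looks 1.8 points better. Death-or-BPD puts it 4.2 points worse.

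**Illustration 2: deaths related to BPD risk.** Assume mortality of 5% v 15%. Infants who would survive in either arm (85%) have BPD risk b of 15% to 35%. The extra 10% who die in one arm would have had BPD risk h, between b and 80%. Differences are the higher-mortality arm minus the other.

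- BPD, all randomised: −0.10·h, from −1.5 points (h = 15%) to −8.0 points (h = 80%).
- BPD, survivors only: 0.10·(b − h)/0.95, from 0 (h = b) to −6.8 points (b = 15%, h = 80%).
- Death or BPD: 0.10·(1 − h), from +8.5 points (h = 15%) to +2.0 points (h = 80%).

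A survivor denominator is therefore unbiased only when death is unrelated to BPD risk.

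**Illustration 3: durations, deaths included.** With 5% v 15% mortality, the difference in means is 0.10·(value in decedents − value in survivors).

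- Length of stay, survivors 50 to 80 days, death at day 5 to 20: from 0.10·(20 − 50) = −3.0 days to 0.10·(5 − 80) = −7.5 days. The sign is always in favour of the arm with more deaths.
- Ventilation time, survivors 3 to 6 days, decedents 2 to 20 days: from 0.10·(2 − 6) = −0.4 days to 0.10·(20 − 3) = +1.7 days. The sign is not fixed.

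**Would the separate survival outcome show the problem?** At 66 per arm, 8% v 14% is about 5 v 9 deaths (66·0.08 = 5.3; 66·0.14 = 9.2), with Fisher p = 0.40. Exact power of Fisher's test is about 13% for 8% v 14% and about 38% for 5% v 15%.

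**The case against.** The strongest reply is that this is a condensed article. It lists outcomes but does not say whether infants who die are scored BPD-free, excluded, censored or treated as a competing event. Such rules are commonly left to a full protocol or analysis plan. That stands as far as analysis rules go, and their absence is no finding. It does not dispose of the outcome definitions, which the article does fix.

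A reader might infer that the plan ignores death altogether. It does not: survival is item (viii) and serious adverse events are reviewed, so an imbalance would be visible. With 66 per arm, however, it could easily be reported as non-significant beside a favourable BPD result.

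A reader might also infer that an arm with more deaths must look better on most secondary outcomes. The working does not support this. The direction is assured only for BPD over all randomised infants and for length of stay. It is probable for oxygen and non-invasive time when deaths are early, and open for ventilation time. For age at autonomy it depends on how deaths are handled.

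Finally, the effect is modest and assumed. A 1.8-point shift is about 1.2 infants in 66, and survivor-only BPD shows no shift under the same inputs. Both statements are correct. The case rests on the possible reversal of direction, which holds at every setting of Illustration 2 when all randomised infants are the denominator.

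**Conclusion.** The point holds for the definitions of items (i) to (v) and (vii). With all randomised infants as denominator, BPD and length of stay are biased towards an arm with more deaths. Under assumed mortality of 5% v 15%, the bias is 1.5 to 8.0 points for BPD and 3.0 to 7.5 days for length of stay, while death-or-BPD runs 2.0 to 8.5 points in the other direction. All these sizes rest on assumed rates.

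Two stronger readings are not supported. One is that the primary outcome is compromised because a first-week death without ventilation counts as a success. That is possible, but unstable infants are excluded and many deteriorating infants would meet the ventilation criteria first. The documents give no frequency, so a sensitivity analysis is enough. The other is that items (iii) and (v) contradict each other because one concerns oxygen only and the other any support. They are different outcomes, and the choice of BPD definition is unrelated to death.

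The change should be made, but it concerns secondary outcomes and leaves the design and sample size intact.

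**What to change.** - **(iii):** change to death before 36 weeks' postmenstrual age or BPD, with both components also reported.
- **(i), (ii), (iv):** report days alive and free of ventilation, oxygen and non-invasive ventilation, in all randomised infants, up to a fixed age that the recorded hospital data cover. A window running past discharge could need follow-up that is not planned. Status at 36 weeks is already needed for (iii), which makes that age a natural candidate.
- **(v), (vii):** analyse as time to event with death as a competing event. In (v), censor infants discharged on support at discharge and report their number by arm, since such censoring may be informative.
- **Primary outcome:** leave it and its 50% planning rate unchanged, because that rate describes intubation and ventilation, not death. Add a pre-specified sensitivity analysis counting first-week death as an event.

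**Cost:** the wording of six secondary outcomes and one added analysis. The survival and support data are already to be recorded, and the sample size does not change. The small downside is that composites are less simple to read and must always be shown with their components.

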**Fig. 1 Fig1:**
[figure not shown]
Schedule of enrolment, interventions, and assessments

The control group infants will perform exclusively the individualized postural care program. They will perform the technique of respiratory facilitation and autogenous drainage modified only in the presence of clinically and radiographically established pulmonary atelectasis.

Both groups will follow the Individualized Family-Centered Developmental Care Program [17]. In particular, attention will be paid to the control of environmental stimuli such as soft lights during treatment to allow the baby to stay awake without being bothered by bright lights directly on the eyes and reduction of environmental noise (tone of the voice of the operators, noise of the monitors, cell phones).

All the interventions of the Individualized Family-Centered Developmental Care are in fact aimed at preventing and containing destabilization and neonatal discomfort considering the extreme sensitivity and vulnerability of these patients to environmental stimulation. In all newborns, the discomfort/pain measurement will be performed, using the Neonatal Pain, Agitation and Sedation Scale (NPASS) [18], according to our NICU protocol.

All patients will receive a loading dose of intravenous caffeine citrate (20 mg/kg) immediately after admission to the NICU, followed by a daily maintenance intravenous dose of 10 mg/kg. Demographic data on patient and maternal characteristics will be collected from each patient. In the two groups of infants, the following parameters will be continuously recorded and analyzed for the entire day, daily in the first week, and weekly after the first week of life: arterial oxygen saturation (SatO2) by Pulse Oximeter Masimo®; heart rate (HR); respiratory rate (RR): inspired fraction of oxygen (FiO2); episodes of apnea defined as cessation of breathing for more than 20 s, or a shorter respiratory pause associated with oxygen desaturation and/or bradycardia; episodes of bradycardia (HR< 80 bpm) or tachycardia (HR > 180 bpm); and secretions’ presence, NPASS Score, Silverman Anderson Score.

In the study group, infants will be also evaluated for vital parameters at T0, at the end of the reflex stimulations and 5 min after the end of the reflex stimulations, and evaluation of behavioral stability of children through the APIB scale (evaluation of preterm infant behavior) [19]. The APIB scale is based on behavioral articles defined according to the “Als Sinactive theory.”

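### Secondary outcome (vi), atelectasis, is open to differential ascertainment, because in this unblinded trial the diagnosis opens access to the technique in the control arm only

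*Protocol article*

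**What the plan says.** All references are to the protocol article.

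- **Outcome.** The Methods section gives secondary outcome (vi) as "Pulmonary atelectasis diagnosed on chest X-ray and/or lung ultrasound".
- **Blinding.** The design paragraph of Methods states: "This will be an unblinded mono-center randomized trial".
- **Study arm.** The technique does not depend on imaging: "This program will be performed 3 times a day until complete respiratory autonomy". The text shown attaches no treatment consequence to an atelectasis diagnosis in this arm.
- **Control arm.** In the paragraph below Fig. 1, control infants have the postural programme alone, and the technique with drainage is "modified only in the presence of clinically and radiographically established pulmonary atelectasis".
- **Abstract.** Its Methods paragraph ends the control-arm description with "They will perform the technique of respiratory facilitation and autogenous drainage" and gives no atelectasis condition.
- **Assessment times.** Fig. 1 is captioned "Schedule of enrolment, interventions, and assessments" and is not shown in the text available. It may or may not list chest imaging.

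**The concern.** The same diagnosis does two jobs. In both arms it is counted as an outcome. In the control arm it is also needed before the infant can have the trial technique. A clinician who knows the allocation and wants physiotherapy for a struggling control infant has a reason to image that infant and to settle an equivocal picture as atelectasis. No matching reason exists in the study arm, where the technique is already being given.

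An outcome that is looked for or read differently in the two arms can differ between them with no true effect. If controls are examined harder, the artefact favours the intervention. Atelectasis bears directly on the claimed mechanism, since the article says the manoeuvre aids lung expansion, so a spurious difference would be easy to read as support for it. This is separate from contamination of the control arm: contamination alters the treatment received, whereas here it is the finding of the outcome that may differ.

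**Working it through.** **1. The rules side by side**

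| | Study arm | Control arm |
|---|---|---|
| Technique given | Three times a day, no imaging condition | Only once atelectasis is established |
| Evidence needed for the technique | None | Clinical and radiographic |
| Evidence needed for outcome (vi) | X-ray, ultrasound or both | The same |
| Allocation known to staff | Yes | Yes |

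What differs by design is the consequence of a diagnosis. Different detection is a plausible result of that, not a stated feature of the design.

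**2. The modality wording.** Read literally, a finding on ultrasound alone counts as outcome (vi) but may not satisfy the control-arm condition, which asks for radiographic and clinical establishment. A treatment condition may be narrower than an outcome definition, so this is not in itself a contradiction, but the article does not say which reading is meant. The abstract omits the condition altogether.

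**3. The plan's own figure.** The article gives no figure for atelectasis. Its only calculation is for the primary outcome, 50% v 25%, two-sided α of 0.05, power 80%:

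- Without continuity correction: n = [1.960·√(2·0.375·0.625) + 0.842·√(0.25 + 0.1875)]² / 0.25² = 57.7, so 58 per arm.
- With correction: n′ = (n/4)·[1 + √(1 + 4/(n·0.25))]² = 65.4, so 66 per arm.

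This reproduces the stated 66. The present point does not touch it; 66 is used below only as the arm size.

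**4. Illustration of size.** The true rate and the detection rates are assumptions. With the same true rate t in both arms and detected fractions s_C (control) and s_S (study), the observed rates are t·s_C and t·s_S, and the apparent relative risk is s_S/s_C whatever t is.

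- t = 15%, 90% v 70%: 0.15·0.90 = 13.5% and 0.15·0.70 = 10.5%; relative risk 0.105/0.135 = 0.78. In infants: 66·0.135 = 8.9 and 66·0.105 = 6.9, about 9 v 7.
- 90% v 80%: relative risk 0.80/0.90 = 0.89.
- Direction reversed (control 70%, study 90%): relative risk 0.135/0.105 = 1.29.

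**5. Chance of a falsely significant difference.** For a pooled two-sided z test, with a and b the observed rates, d = a − b, m = (a + b)/2, se0 = √[2m(1 − m)/66] and se1 = √{[a(1 − a) + b(1 − b)]/66}:

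P = Φ[(d − 1.96·se0)/se1] + Φ[(−d − 1.96·se0)/se1].

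Example with t = 20%, 90% v 70%: a = 0.18, b = 0.14, se0 = 0.0638, se1 = 0.0637; P = Φ(−1.34) + Φ(−2.59) = 0.096.

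| True rate in both arms | 90 v 90% | 90 v 80% | 90 v 70% | 90 v 60% |
|---|---|---|---|---|
| 10% | 0.050 | 0.055 | 0.071 | 0.100 |
| 20% | 0.050 | 0.061 | 0.096 | 0.161 |
| 30% | 0.050 | 0.068 | 0.127 | 0.235 |
| Apparent relative risk | 1.00 | 0.89 | 0.78 | 0.67 |

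Swapping the arms gives the same probabilities with the relative risk inverted.

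**The case against.** The strongest reply is that most of the chain is conjecture about behaviour. The article does not say who orders or reads chest images, when, or by what criterion. Fig. 1 may hold an imaging schedule, and a condensed article normally leaves such details to the full protocol, so their absence is no fault. This stands: the point cannot rest on missing imaging detail. It rests on two things the article does state, the open design and a treatment rule tied to the outcome diagnosis in one arm. A common schedule would reduce the problem, but would not by itself prevent extra unscheduled images or unblinded reading.

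The direction may also be the opposite. Study infants see a physiotherapist three times a day, have vital signs checked around each stimulation, and have behavioural assessment. That extra observation could raise detection in the study arm. This stands too.

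A reader might infer that detection differs between the arms by design, that unblinded staff order the images, or that a positive image alone gives a control infant the technique. The documents support none of these. Only the consequence of a diagnosis differs by design; image ordering is not described; and the rule requires clinical establishment as well as the image.

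Finally, the illustrated effect is small, about two infants, and concerns one of eight secondary outcomes. That limits the weight of the point but does not remove it.

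**Conclusion.** The concern holds in a limited form. Outcome (vi) is open to differential ascertainment, because an unblinded team works under a rule that makes the diagnosis matter for access to the technique in one arm only. Neither size nor direction follows from the document. On assumed true rates of 10% to 30% and detection of 90% in controls against 60% to 90% in the study arm, the apparent relative risk runs from 0.67 to 1.00 and the chance of a falsely significant result from 5% to about 24%; the ratios invert if detection is better in the study arm. These figures show what could happen and are not estimates for this trial. The primary outcome and the sample size are unaffected, so this is a cheap improvement to one secondary outcome and not a defect in the trial's main comparison.

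**What to change.** - Apply one stated atelectasis criterion in both arms.
- Take outcome (vi) from existing image reports made with allocation left off the request. Flag bedside ultrasound findings read by unblinded staff separately instead of discarding them, since the outcome expressly accepts ultrasound.
- Record the number of chest images per infant and the reason for each, report both by arm, and interpret outcome (vi) in that light.
- State whether an ultrasound-only finding meets the control-arm condition, so that the outcome list, the control-group paragraph and the abstract are reconciled. Which condition applies is for the sponsor to decide.
- Do not add a sensitivity analysis that removes images taken to qualify control infants for the technique. It would be an exclusion after randomisation in one arm only, would drop true control cases, and could bias the comparison the other way.

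If Fig. 1 or the full protocol already sets common imaging criteria and masked reading, it is enough to say so and to reconcile the wording.

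Cost: protocol wording, a neutral imaging request and slightly more data collection. No additional images are needed; that no additional reader is needed assumes that routine image reports exist, which the article does not say. Masked reading does not remove differences in how often images are ordered; the counts by arm expose these but do not correct them.
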